#### Summary of known and potential risks of the study drug

All three study medications are approved by the EMA for vaccination against SARS-CoV-2 in individuals over 16 years of age. Overall safety profiles are excellent with over a billion doses administered worldwide as of May 19, 2021 (ourworldindata.org). An overview of undesirable effects and respective frequencies for each study drug are reported below:

#### COVID-19 Vaccine Moderna [mRNA-1273, Moderna]:

| System organ class                   | undesirable effect            | Frequency   |
|--------------------------------------|-------------------------------|-------------|
| Blood and lymphatic system disorders | Lymphadenopathy               | very common |
| Immune system disorders              | Anaphylaxis, Hypersensitivity | unknown     |

|                                                      |                                                                                 |                |
|------------------------------------------------------|---------------------------------------------------------------------------------|----------------|
| Nervous system disorders                             | Cephalaea                                                                       | very
common |
|                                                      | Acute Peripheral facial palsy                                                   | rare           |
| Gastrointestinal disorders                           | Nausea/Emesis                                                                   | very
common |
| Skin and subcutaneous tissue disorders               | Rash                                                                            | common         |
| Musculoskeletal and connective tissue disorders      | Myalgia, Arthralgia                                                             | very
common |
| General disorders and administration site conditions | Pain at Injection site, Tiredness, Chills, Fever, Swelling at injection site    | very
common |
|                                                      | Erythema at Injection site, Urticaria at injection site, Rash at injection site | common         |
|                                                      | Itching at injection site                                                       | uncommon       |
|                                                      | Facial swelling                                                                 | rare           |

## Comirnaty [BNT162b2, PfizerBioNTech]

| System organ class                   | undesirable effect            | Frequency |
|--------------------------------------|-------------------------------|-----------|
| Blood and lymphatic system disorders | Lymphadenopathy               | uncommon  |
| Immune system disorders              | Anaphylaxis, Hypersensitivity | unknown   |
| Psychiatric disorders                | Sleeplessness                 | uncommon  |

|                                                      |                                                                                      |                |
|------------------------------------------------------|--------------------------------------------------------------------------------------|----------------|
| Nervous system disorders                             | Cephalaea                                                                            | very
common |
| Gastrointestinal disorders                           | Nausea                                                                               | common         |
| Skin and subcutaneous tissue disorders               | Arthralgia, Myalgia                                                                  | very
common |
|                                                      | Pain in the extremities                                                              | uncommon       |
| General disorders and administration site conditions | Pain at the injection site, tiredness, chills, fever, swelling at the injection site | very
common |
|                                                      | Redness at injection site                                                            | common         |
|                                                      | Malaise, itching at injection site                                                   | uncommon       |

#### COVID-19 Vaccine Janssen [Ad26.COV2-S, Johnson&Johnson]

| System organ class                     | undesirable effect           | Frequency   |
|----------------------------------------|------------------------------|-------------|
| Immune system disorders                | Hypersensitivity, Urticaria  | rare        |
| Nervous system disorders               | Anaphylaxis                  | not known   |
|                                        | Headache                     | very common |
|                                        | Tremor                       | uncommon    |
| Respiratory, thoracic and mediastinal  | Cough                        | common      |
|                                        | Sneezing, oropharyngeal pain | uncommon    |
| Gastrointestinal disorders             | Nausea                       | common      |
| Skin and subcutaneous tissue disorders | Rash                         | uncommon    |
|                                        | Myalgia                      | very common |

|                                                      |                                                                       |             |
|------------------------------------------------------|-----------------------------------------------------------------------|-------------|
| Musculoskeletal and connective tissue disorders      | Arthralgia                                                            | common      |
|                                                      | Muscular weakness, back pain, limb pain                               | uncommon    |
| General disorders and administration site conditions | Tiredness, pain at injection site                                     | very common |
|                                                      | Fever, erythema at injection site, swelling at injection site, chills | common      |
|                                                      | Asthenia, malaise                                                     | uncommon    |

Very common:  $\geq 1/10$

Common:  $\geq 1/100$  to  $< 1/10$

Uncommon:  $\geq 1/1,000$  to  $< 1/100$

Rare:  $\geq 1/10,000$  to  $< 1/1,000$

Very rare:  $< 1/10,000$

Not known: cannot be estimated from the available data

## 8. Statistical analysis

### Sample size calculation

For testing the primary study endpoint (positive antibody to the SARS-CoV-2 vaccine) we assume a response rate of 30% and 50% in the mRNA and the viral vector-based vaccine treatment arms and expect a dropout rate of a maximum of 5%. Currently, no data on a third vaccination in kidney transplant recipients exist. The 30% response rate for the homologous vaccination group has been chosen expecting a slightly lower response rate to the third vaccination in kidney transplant recipients who did not respond to the standard 2-dose vaccination regime compared to the initial response rate of kidney transplant recipients to

the standard 2-dose vaccination regime (37% response rate). The 50% response rate estimate for the heterologous vaccination groups is based on early data from studies investigating heterologous vaccination which showed a higher reactogenicity after the heterologous vaccination. Enrollment of 100 patients per group will provide 80% power (alpha-error: 5%) to detect a difference in response between the two treatment groups.

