| Visits                         | Number | 1                                   | 2         | 3                                   | 4                                   | 5                                    | 6                                      | 7                                      |
|                                | Name   | Screening                           | Treatment | Follow up 1                         | Follow up 2                         | Follow up 3                          | Follow up 4                            | Follow up 5                            |
|                                | Time   | within 28 days prior to vaccination | Day 1     | Day 29-42 (4 weeks after treatment) | Day 57-70 (8 weeks after treatment) | Day 85-98 (12 weeks after treatment) | Day 168-196 (24 weeks after treatment) | Day 336-364 (48 weeks after treatment) |
| Informed consent               |        | x                                   |           |                                     |                                     |                                      |                                        |                                        |
| Inclusion / Exclusion Criteria |        | x                                   |           |                                     |                                     |                                      |                                        |                                        |
| Medical History                |        | x                                   |           |                                     |                                     |                                      |                                        |                                        |
| Concomitant medication         |        | x                                   |           |                                     |                                     |                                      |                                        |                                        |
| SARS-CoV-2 Antibodies          |        | x                                   |           | x                                   | x                                   | x                                    | x                                      | x                                      |

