### 3. Background

Kidney transplant recipients are at high risk for a severe COVID-19 disease course and therefore prioritized to receive early vaccination against SARS-CoV-2 (1, 2). In general, the immune response to vaccination is reduced in immunosuppressed individuals including kidney transplant recipients. A recent study from Israel confirmed that only 37.5% of kidney transplant recipients developed detectable antibodies against the spike protein following full vaccination with BNT162b2 (Pfizer-BioNTech) (3). The type of maintenance immunosuppression may have a significant impact on the immune response in kidney transplant recipients. Patients treated with co-stimulation blockade (Belatacept) as maintenance immunosuppression showed even lower immunization rates of only 5.7 % (4).

Several strategies have been proposed to improve response to SARS-CoV-2 vaccination including additional dosing and mixing different vaccine types to broaden the presented antigen repertoire (heterologous vaccination or “mix-and-match strategy”) (5). Recent data show a higher reactogenicity of heterologous boosting in the general population (6). In the European Union there are currently two different classes of SARS-CoV-2 vaccines available: a) mRNA (mRNA-1273 [Moderna Biotech] and BNT162b2 [Pfizer-BioNTech]) and b) viral vector-based vaccines (ChAdOx1 [AstraZeneca] and Ad26COVS1 [Jansen]). Of these Ad26COVS1 is the only vaccine that has been shown to induce a protective immune response after a single dose (7). Kidney transplant recipients in Austria have primarily been vaccinated with mRNA-based vaccines.

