### Benefit and risk assessment

Patients with immunosuppression are considered to be at great risk for a severe disease course of COVID-19 an additional vaccination will increase their chance to develop a protective immune response. The risk for adverse events following a third vaccination is low compared to the risk associated with a SARS-CoV-2 infection in this population. All study drugs have been approved by the European Medicines Agency (EMA).

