### Reporting procedures for all Adverse Events

The investigator is responsible for ensuring that all adverse events (as defined above) observed by the investigator or reported by subjects are properly captured in the subjects’ medical records.

In addition, the investigator is responsible for ensuring that, for those subjects randomized into the study, all adverse events captured on the subjects’ medical records (as specified

above) are reported on the case report form. This collection period will be from the time of administration of the study drug until the end of the study.

The following adverse event attributes must be assigned by the investigator:

- adverse event diagnosis or syndrome(s) (if known, signs or symptoms if not known)
- event description (with detail appropriate to the event)
- dates of onset and resolution
- severity
- assessment of relatedness to investigational product
- action taken

The relationship of the adverse event to the investigational product will be assessed by means of the question: “Is there a reasonable possibility that the event may have been caused by the investigational product?” The investigator should respond to this question with either Yes or No.

Medically significant adverse events considered related to the investigational product by the investigator will be followed until resolved or considered stable.

Adverse events will be reported in the publication arising from this study.

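### Higher reactogenicity is used to support the 50% antibody response in the vector arm, is not carried into the risk sections, and early reactions are not actively collected between the vaccination day and Day 29-42

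*Protocol*

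**What the plan says.** - **Planning rates.** In the protocol's Sample size calculation, "we assume a response rate of 30% and 50% in the mRNA and the viral vector-based vaccine treatment arms". The 30% is set a little below a 37% antibody response to two doses. The 50% is "based on early data from studies investigating heterologous vaccination which showed a higher reactogenicity after the heterologous vaccination".
- **Background (section 3).** "Recent data show a higher reactogenicity of heterologous boosting in the general population (6"). The reference list shows source 6 to be, by its title, early reactogenicity data on heterologous prime-boost vaccination. The other heterologous source, reference 5, is a mouse study.
- **Benefit and risk assessment.** "The risk for adverse events following a third vaccination is low compared to the risk associated with a SARS-CoV-2 infection in this population". Nothing here is specific to a heterologous dose.
- **Summary of known and potential risks (section 7).** There is a separate side-effect table for each of the three products and no entry for the heterologous sequence.
- **Adverse event timing.** Table 1 and the Clinical data section schedule an assessment at visit 2 (Day 1, the vaccination day). The next is at visit 3, which Table 1 labels "Day 29-42 (4 weeks after treatment").
- **Adverse event collection.** Section 7 collects events from dosing to the end of the study, whether seen by the investigator or reported by the patient, with onset and resolution dates and severity. It adds: "Adverse events will be reported in the publication arising from this study".
- **Blinding.** Study design states that only the patient is blinded.

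**The concern.** Three things follow from one word.

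First, reactogenicity covers fever, chills, pain, tiredness and the like. A vaccine sequence can cause more of these without producing antibodies in more patients, so the stated basis does not support the 50%. That figure is half of the assumed treatment difference, and power depends strongly on it.

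Second, the same observation is a tolerability signal for the mix-and-match arm, yet the sections where a reader looks for risk do not carry it.

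Third, the trial is meant to guide a choice between two strategies that its own Background says may differ in reactions, and it undertakes to publish adverse events. Most reactions to an injection would be expected in the first days, when no study assessment is scheduled and no diary or solicited list is described. What is recorded then depends on who volunteers a report and on what is remembered at visit 3. Staff who ask about those weeks and judge severity and relatedness may know the arm.

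**Working it through.** **1. Reproducing the plan's sample size.** Inputs from the Sample size calculation and Randomization sections: p1 = 0.30, p2 = 0.50, alpha 5%, power 80%, 1:1 allocation, dropout up to 5%. Sidedness is not stated; two-sided is taken here.

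n per arm = [1.960·√(2·p̄·(1−p̄)) + 0.842·√(p1(1−p1) + p2(1−p2))]² / (p2−p1)², with p̄ = 0.40

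- 1.960·√0.48 = 1.358
- 0.842·√0.46 = 0.571
- (1.358 + 0.571)² / 0.04 = 3.72 / 0.04 = 93 per arm
- With dropout: 93 / 0.95 = 97.9, so 98 per arm, against 100 stated

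With 100 enrolled and 5% lost, 95 per arm are evaluable. Power is then 80.8% by the normal approximation and 80.6% by exact enumeration of the uncorrected chi-squared test. The stated 80% is right for the stated inputs.

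**2. How much rests on the 50%.** Control rate 30%, 95 evaluable per arm, two-sided 5%. The alternative vector-arm rates are my assumptions, because the document gives none.

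Power = Φ{[(p2−p1)·√n − 1.960·√(2p̄(1−p̄))] / √(p1(1−p1)+p2(1−p2))}

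| Assumed vector-arm rate | Power at 95 per arm | Evaluable per arm for 80% |
|---|---|---|
| 50% (plan) | 81% | 93 |
| 47.5% | 70% | 121 |
| 45% | 57% | 163 |
| 40% | 30% | 356 |

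For 45%: (0.15·9.747 − 1.342) / 0.676 = 0.178, and Φ(0.178) = 0.57.

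**3. Risk statements side by side.** The Background says heterologous boosting showed more reactions. The product tables in section 7 give these classes:

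| Reaction | mRNA-1273 | BNT162b2 | Vector vaccine |
|---|---|---|---|
| Fever | very common | very common | common |
| Chills | very common | very common | common |
| Arthralgia | very common | very common | common |
| Swelling at injection site | very common | very common | common |

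Very common means at least 1 in 10; common means at least 1 in 100 but below 1 in 10. The tables describe each product, not a vector dose after two mRNA doses, so they do not refute the Background. But someone reading only the risk sections could conclude that the vector arm is the milder one, the opposite of the Background's signal.

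**4. The gap in scheduled assessment.** Visit 2 is Day 1 and visit 3 is Day 29 to 42. 29 − 1 = 28 days and 42 − 1 = 41 days, so recall at visit 3 reaches back about 4 to 6 weeks. The size of the recall loss cannot be calculated: the document has neither reaction rates for the heterologous sequence nor any figure for forgetting.

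**The case against.** The strongest reply is that little depends on this. The protocol already presents the 30% and 50% as assumptions and says no data on a third dose in kidney transplant recipients exist. Rewording the basis of the 50% changes neither the sample size nor the test. Tolerability is neither an objective nor an endpoint, so a diary is an addition and not the repair of an error. Adverse events are collected continuously with dates and severity, patients can report at any time, and the Follow-up section describes routine clinic visits outside the study schedule. All of that stands, and it limits the weight of the point. It does not make reactogenicity evidence of antibody response. Nor does it supply active, uniform collection in the first days: routine visits are not tied to the injection date, and spontaneous report differs from patient to patient.

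Several stronger readings are tempting, and the document does not support them:

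- *A reader might infer that adverse events are first asked about at Day 29-42.* They are also assessed at visit 2, and reports are accepted throughout.
- *That the vector arm is presented as carrying the same risk as the mRNA arm.* The benefit-risk text compares a third dose with infection, and each product has its own table.
- *That most listed reactions are very common, so every symptom will yield many events.* For the vector vaccine only 4 of 23 listed terms are in that class: headache, myalgia, tiredness and injection-site pain.
- *That the visit schedule results from misunderstanding reactogenicity.* Nothing in the text links the two.
- *That patients are not told.* The patient information is not shown, so this cannot be judged. The case report form is not shown either, and may contain symptom prompts.

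**Conclusion.** The point holds in three limited parts.

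1. The 50% has no immunogenicity data behind it in the document, and the reason given concerns side effects. A reader might infer that the sample size is wrong; it is not, since 98 per arm is reproduced against 100 stated. What is exposed is power, which falls to about 57% or 30% if the vector-arm rate is 45% or 40%. Those rates are assumed, with a 30% control rate and 95 evaluable per arm.
2. The Background and the risk sections are not aligned on the reactogenicity of the heterologous sequence and must be reconciled.
3. Early reactions are measured by spontaneous report or by recall over 28 to 41 days, with staff not blinded. This weakens the by-arm tolerability comparison that the protocol undertakes to publish. It does not make it uninterpretable: if forgetting is similar in both arms, for example, the ratio between arms is largely kept. This part assumes that no symptom prompts or early contacts exist in materials not shown.

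The primary endpoint and its analysis are unaffected. The change is worth making because it is cheap and improves data that will be reported anyway.

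**What to change.** - **Symptom card.** At visit 2 give each patient a one-page card covering 7 days, listing the local and systemic reactions already named in the section 7 product tables. Collect it at visit 3 and report the results by arm. Completed at the time by the blinded patient, it reduces dependence both on recall and on questioning by staff who may know the arm. Cost: one paper form at visits already planned, with a small burden on patients and data entry.
- **Sample size calculation.** Call the 50% a planning assumption without immunogenicity data and drop reactogenicity as its basis. Cost: one sentence; the number of patients is unchanged.
- **Risk text.** Reconcile the Benefit and risk assessment and the section 7 risk summary with the Background statement on heterologous boosting, making clear that the product tables do not describe the heterologous sequence. Check that the patient information says the same. Cost: wording only.

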### Endpoint analysis

For all endpoints a per protocol analysis will be carried out.

For the primary endpoint (positive humoral immune response to SARS-CoV-2 vaccination at 4 weeks after the vaccination) SARS-CoV-2 S IgG antibody test results will be recorded and counts and percentages of patients exceeding the manufacturer defined cutoff of 0.8U/ml in each treatment arm will be reported. A chi-squared test will be employed to test for statistically significant differences in the number of responders (antibody concentration exceeds the manufacturer defined cutoff of 0.8U/ml) between the treatment arms.

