## Primary objective (Hypotehsis)

We specifically hypothesize that a single dose of the viral vector-based vaccine Ad26COVS1 [Jansen] results in a higher rate of antibody response compared to a third dose of the previously used mRNA vaccine (mRNA-1273 [Moderna Biotech] or BNT162b2 [Pfizer-BioNTech]).

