## 5. Study design

This is a single center, single blinded, randomized study. Only the patient will be blinded for the type of vaccine administered. Based on sample-size calculations (see below) a total of 200 patients will be enrolled into the study.

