### Withdrawal of subject

Subjects may prematurely discontinue from the study at any time. Subjects must be withdrawn under the following circumstances:

- at their own request
- if the Investigator feels it would not be in the best interest of the subject to continue
- if the subject violates conditions laid out in the consent form / information sheet or disregards instructions by the study personal

In all cases, the reason why subjects are withdrawn must be recorded in detail in the CRF

Should the study be discontinued prematurely, all study materials (completed, partially completed and empty CRFs) will be retained.

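### Per protocol is the stated analysis for every endpoint, including the primary superiority test, and the protocol plans no as-randomised analysis

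*Protocol*

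**What the plan says.** Protocol section 8 (Endpoint analysis) opens with the analysis population: "For all endpoints a per protocol analysis will be carried out". The primary test follows directly: "A chi-squared test will be employed to test for statistically significant differences in the number of responders". No section names an intention-to-treat, full-analysis or as-randomised set, or a sensitivity analysis on another population. The per-protocol set itself is not defined.

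The hypothesis in section 4 is one of superiority, namely that the vector vaccine "results in a higher rate of antibody response compared to a third dose of the previously used mRNA vaccine".

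Three features of section 6 and one of section 5 bear on who might be excluded:

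- Randomisation takes place once the antibody status is known, and the vaccination appointment is given afterwards (Randomization; Treatment).
- Withdrawal is mandatory if the investigator judges that continuing is not in the patient's best interest (Withdrawal of subject).
- It is also mandatory "if the subject violates conditions laid out in the consent form / information sheet or disregards instructions by the study personal" (same section).
- On blinding, section 5 says: "Only the patient will be blinded for the type of vaccine administered".

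The sample size section allows for at most 5% dropout. The closing paragraph of section 8 foresees an update of the analysis plan, but only to add stratification.

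**The concern.** In a superiority trial, randomisation protects the comparison of all patients in the arms to which they were assigned. A per-protocol set depends on what happens after randomisation: whether the patient came for the injection, stayed in the study, and was judged compliant. If these events are related to both the arm and the chance of response, the difference is biased, and the chi-squared test no longer has its stated 5% error rate.

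The protocol leaves room for this. A patient can be lost between randomisation and dosing. Two of the withdrawal reasons are staff judgements, made by people who are not blinded. Because the set has no definition, exclusions could also be decided after the visit 3 antibody result is known. At stake is the only confirmatory test in the trial, since the secondary analyses are declared exploratory.

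**Working it through.** **Inputs.** The sample size section gives the rates: "we assume a response rate of 30% and 50% in the mRNA and the viral vector-based vaccine treatment arms". It also gives 100 patients per arm, alpha 5%, 80% power and at most 5% dropout. Allocation is 1:1. Sidedness is not stated; two-sided is assumed, without continuity correction.

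**1. The protocol's own figure.** With p1 = 0.30, p2 = 0.50 and mean 0.40:

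n = [1.960 × √(2 × 0.40 × 0.60) + 0.842 × √(0.30 × 0.70 + 0.50 × 0.50)]² / 0.20² = (1.358 + 0.571)² / 0.04 = 93 per arm.

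Allowing for 5% loss, 93 / 0.95 = 98, against 100 planned. With 95 evaluable per arm, power is 80.8% by the normal formula and 80.6% by exact binomial enumeration of the chi-squared test. The stated 80% is reproduced, so the sample size is not the problem.

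**2. The two populations at the planned effect.** Lose 5 patients per arm and take 28/95 against 48/95 responders (29.5% and 50.5%).

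| Analysis | Responders | Difference | p |
|---|---|---|---|
| Per protocol | 28/95 vs 48/95 | 21.1 points | 0.003 |
| As randomised, missing = non-response | 28/100 vs 48/100 | 20.0 points | 0.004 |
| Worst case: lost mRNA patients respond, lost vector patients do not | 33/100 vs 48/100 | 15 points | 0.031 |
| Opposite extreme | 28/100 vs 53/100 | 25 points | 0.0003 |

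All four are significant at 5%.

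**3. A smaller observed effect.** Per protocol, 30/95 vs 44/95 gives p = 0.037. As randomised with missing as non-response, 30/100 vs 44/100 gives p = 0.040. In the worst case, 35/100 vs 44/100 gives p = 0.19. The proposed rule leaves the conclusion unchanged here; only the extreme case alters it.

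**4. Type I error.** Suppose both arms truly respond at 30%, one arm loses 5 responders and the other loses 5 non-responders. The expected per-protocol rates are 25/95 = 26.3% and 30/95 = 31.6%. Drawing responders from Binomial(100, 0.30) in each arm, removing the 5 patients and enumerating the test on 95 per arm gives a rejection rate of 13.6%. Drawing instead from Binomial(95, 25/95) and Binomial(95, 30/95) gives 12.5%. Without selective loss it is about 5%.

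**5. Power of the as-randomised analysis.** With 5% loss counted as non-response, the rates are 0.95 × 30% = 28.5% and 0.95 × 50% = 47.5% on 100 per arm. Exact power is 79.7% (normal formula 79.5%), against 80.6% per protocol. By the normal formula, 102 per arm would give a full 80%.

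**The case against.** The case on the other side has real weight.

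- **Little room for selection before visit 3.** Treatment is one injection at the clinic, so there is no continuing adherence to judge. The endpoint is a laboratory value against a fixed cutoff. Visit 3 is the first scheduled antibody sample after dosing, so on schedule an investigator who withdraws a patient earlier may know the arm but not the antibody response. This stands. It does not cover patients lost between randomisation and dosing, or exclusions decided after visit 3.
- **The mechanism is partly inferred.** The withdrawal section lists reasons for leaving the study and does not define the per-protocol set. This is correct; the text permits such exclusions without saying that they will be made.
- **The bounds are extreme.** If loss is unrelated to response, all five lost mRNA patients being responders and all five lost vector patients being non-responders has probability 0.3⁵ × 0.5⁵, about 0.00008. The 15 to 25 point range is therefore a limit, not a forecast.
- **Non-response imputation is itself an assumption.** Renaming the population does not recover results that were never measured. This also stands, and is why the withdrawal section matters: a result that is collected needs no imputation.

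A reader might also infer that no as-randomised result will ever exist. The sentence does not say that per protocol is the only analysis, and a separate analysis plan, not shown here, could add another. What can be said is that this protocol plans none. A reader might further infer that the bias will favour finding a difference. Nothing in the document fixes the direction.

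**Conclusion.** The point holds as a stated choice that does not suit a superiority question: the protocol names per protocol for the primary test and plans no as-randomised comparison. This is not a detail left open for the analysis plan, because the protocol has already made the choice.

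The expected harm is modest. Within 5% loss unrelated to response, the two analyses differ by about 1 point. The larger figures (15 to 25 points, and a type I error of about 14%) require fully selective loss of 5 patients per arm, with opposite selection in the two arms for the type I error and for the 15 and 25 point ends. It would go beyond the evidence to infer that the primary conclusion is likely to be wrong. The results assume a two-sided test without continuity correction and the protocol's own response rates and dropout ceiling. The change should be made, because the defect governs the sole confirmatory test and the remedy is cheap.

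**What to change.** 1. **Primary analysis.** Change the opening sentence of Endpoint analysis so that the chi-squared test includes all randomised patients in the arm assigned, with a missing visit 3 antibody result counted as non-response. Keep per protocol as a supportive analysis.
2. **Binary secondary endpoints.** Apply the same rule to the later humoral responder endpoints and the cellular responder endpoint.
3. **Continuous endpoints.** Analyse antibody and IFN-γ concentrations by arm assigned on available data. Non-response imputation has no meaning for t-tests on log values.
4. **Infection counts.** Report them by arm assigned.
5. **Withdrawal of subject.** Reconcile this section with the new population, so that withdrawal by staff judgement does not by itself remove a consenting patient's results from the analysis. As written, mandatory withdrawal for disregarding instructions conflicts with obtaining those results.

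The cost is protocol wording, an amended withdrawal section, and a second run of the tests. Power at 5% loss falls from 80.6% to 79.7%, so the stated 80% should read as about 80%. The estimate is diluted by about 1 point. The sample size need not change.
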